## Blinding assessment

The previous studies have shown that the experience of the sensations induced by tDCS are usually fade out after 30 seconds; thus, we will use this period in the sham tDCS group, to evaluate the blinding quality of the study design, after completion of the intervention we will ask the patients whether they know which type of stimulation, real or sham tDCS, they received. This assessment will be performed after each tDCS session in all groups. 

***Adverse effects and tolerability***

Previous studies have reported no severe AEs of tDCS for different protocols. However, most of the previous studies used single session tDCS. For this study, considering the multisession protocol of tDCS, the AEs of and tolerability to the repeated sessions of tDCS will be assessed using a customized questionnaire (
Supplementary File 1) which will be applied after the last session.

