## Abstract

**Background**: Transcranial Direct Current Stimulation (tDCS) is reportedly a potential treatment option for chronic tinnitus. The main drawbacks of previous studies are short term follow up and focusing on the efficacy of single session tDCS. This study aims to investigate the therapeutic efficacy, adverse effects (AEs) and tolerability of repeated sessions of bilateral tDCS over auditory cortex (AC) on tinnitus symptoms

**Methods**: This will be a double-blinded randomized placebo controlled parallel trial on patients (n=90) with intractable chronic tinnitus (> 2 years) randomly divided into three groups of anodal, cathodal, and sham tDCS. In the sham treatment, after 30 sec the device will be turned OFF without informing the patients. The tDCS protocol consists of 10 sessions (daily  20 min session; 2 mA current for 5 consecutive days per week and 2 consecutive weeks) applied through 35 cm
^2^ electrodes. The primary outcome is tinnitus handicap inventory (THI) which will be assessed pre- and post-intervention and at one month follow-up. The secondary outcomes are tinnitus loudness and distress to be assessed using a visual analogue scale (VAS) pre-intervention, and immediately, one hour, one week, and one month after last stimulation. The AEs and tolerability of patients will be evaluated after each session using a customized questionnaire. Possible interactions between the disease features and treatment response will be evaluated.

**Discussion**: To our knowledge this is the first study to investigate the effects of repeated sessions of tDCS on chronic tinnitus symptoms with one month follow-up. In addition, the AEs, and tolerability of patients will be studied. In addition, the possible interactions between the disease specific features including the hearing loss, laterality, type of tinnitus, and treatment response will be evaluated.

**Trial registration**: The study has been registered as a clinical trial in Iranian Registry of Clinical Trial (
IRCT2016110124635N6) on the 01/06/2017.

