### Inclusion and exclusion criteria

The patients should meet specific criteria for inclusion in this project. The primary criteria will be evaluated during the neurological and otolaryngological examinations by experienced specialists. The patients will be selected among the tinnitus patients referred to the Tinnitus Clinic in the Khuzestan Cochlear Implant Center, Ahvaz, Iran. After the start of the study and anytime during the study, patients have the right to leave the study. In case of any significant adverse effects (AEs), the procedures for the respective patients will be terminated.

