### Transcranial direct current stimulation protocol

The direct current will be applied through a saline-soaked pair of surface electrodes (35 cm
^2^) and delivered by a tDCS device which is a specially developed, battery-driven, constant current stimulator with a maximum output of 2 mA. The tDCS device used in this study will be an OASIS Pro
^TM^ device by Mind Alive Inc (Edmonton, Alberta, Canada). Anodal and cathodal tDCS groups will consist of daily 20-min sessions of 2 mA current for five consecutive days per week and for 2 consecutive weeks (10 sessions in total). In anodal tDCS, the anode and cathode will be respectively centered over left AC (halfway T3 - F7) and right AC (halfway T4 - F8). In the cathodal tDCS the electrodes position will be reversed where cathode and anode will be respectively centered over left AC (halfway T3-F7) and right AC (halfway T4-F8). The site of electrodes will be selected according to the
International 10-20 electroencephalography system. In the sham tDCS group, the electrode montage will be the same as the anodal tDCS, but the device will be turned off after 30 s without the knowledge of the participant. These parameters for sham stimulation were chosen based on previous reported findings where the perceived sensations of stimulation on the skin, such as tingling, usually disappear in the first 30 s of active tDCS
^23,
26^ (
Table 1).

**Table 1. T1:** Setting for anodal, cathodal, and sham Transcranial Direct Current Stimulation (tDCS).

	Anodal tDCS	Cathodal tDCS	Sham tDCS
Current density	57.1 µA/cm ^2^	57.1 µA/cm ^2^	57.1 µA/cm ^2^
Electrode montage	Anode left (halfway T3 - F7) and cathode right AC (halfway T4 - F8)	Cathode left (halfway T3 - F7) and anode right AC (halfway T4 - F8)	Anode left (halfway T3 - F7) and cathode right AC (halfway T4 - F8)
Duration	20 min	20 min	20 min ^*^

Note: * 30 seconds after the start of the stimulation the device will be turned off without the knowledge of patient.

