### Adverse effects and tolerability

The previous studies on the safety and tolerability of tDCS have shown that the 2 mA current applied in 20 minutes are associated with no serious AEs
^24,
26^. The common reported AEs are itching or tingling sensation, mild headache or fatigue and local burns at the site of stimulation. However, most of the AEs and tolerability assessments have been performed on the tDCS were for single session ranging 20–30 minutes and current of 1 to 2 mA. In our study, we will use repeated sessions of tDCS (2 mA current for 20 minute, total 10 sessions, daily one session, five consecutive days per week and 2 consecutive weeks), thus the reported AEs in the previous studies may be intensified. Therefore, we will assess the AEs using a customized questionnaire (
Supplementary File 1). The questionnaire will be performed during and after each tDCS session to record all the perceived AEs from the patients in all three tDCS groups.

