### Outcomes assessments

The primary and secondary outcomes will be measured in two main time points: pre- and post-intervention. The pre-intervention assessments of the outcomes will be performed at the first day of the intervention before tDCS stimulation (T
_1_). There will be four time points of post-intervention assessments as T
_2_, T
_3_, T
_4_, and T
_5_ corresponding to the immediately after last session, one hour, one week, and one month after last tDCS session.
Table 2 represents the SPIRIT schematic protocol of the study and timing of the assessments.

**Table 2. T2:** Standard Protocol Items: Recommendations for Interventional Trials of this study.

	Enrolment	Allocation	Pre- intervention	Intervention	Post- intervention			
TIME POINT	*-T _1_*	T _0_	*T _1_*		*T _2_*	*T _3_*	*T _4_*	*T _5_*
ENROLMENT:								
Eligibility screen	X							
Informed consent	X							
*Demographic* *information*	X							
Allocation		X						
INTERVENTIONS:								
*real (anodal and* *cathodal) tDCS*								
*Sham tDCS*								
ASSESSMENTS:								
*Neurological* *and audiological* *assessments*	X							
*Hearing loss* *assessment*	X							
*Primary outcome:* *THI*			X		X			X
*Secondary outcomes:* *loudness*			X		X	X	X	X
*Distress*			X		X	X	X	X
*AEs and Tolerability*					X			

Note: THI: tinnitus handicap inventory; AEs: adverse effects, -T
_1_: one month before intervention, T
_0_: one day before intervention, T
_1_: 5 min before intervention, T
_2_: immediately after last session, T
_3_: at hour after last session, T
_4_: one week, and T
_5_: at month after last tDCS session. Real tDCS refers to anodal and cathodal tDCS groups.

***Primary outcome***. Tinnitus handicap inventory (THI) score will be the primary outcome. The THI is a 25-item questionnaire and commonly used as self-reporting inventory for disabling level of tinnitus. The THI items are grouped into three subscales: Functional (11 items), emotional (9 items), and catastrophic (5 items) subscales. Each item is three point Likert type scale with three alternative assessments: yes (4 points), sometimes (2 points), and no (0 point). The questionnaire yields scores for each subscale and a total score that ranges 0 to 100, where higher score means more severe tinnitus or a greater handicap

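### The adverse-effect questionnaire is scheduled at every session in two places but after the last session in two others, and the later schedule could miss patients who stop early

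*Protocol article*

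**What the plan says.** Four places in the protocol article give a time for AE assessment.

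- Abstract, Methods: "The AEs and tolerability of patients will be evaluated after each session using a customized questionnaire".
- Adverse effects and tolerability, in the Methods after the stimulation protocol: "The questionnaire will be performed during and after each tDCS session to record all the perceived AEs". This covers all three groups. The reason given is that earlier safety data come mostly from single sessions, so effects may be stronger with repetition.
- Adverse effects and tolerability, in the outcomes part after the blinding assessment: the same customized questionnaire (Supplementary File 1), "which will be applied after the last session".
- Table 2 (Outcomes assessments): the row "AEs and Tolerability" has one mark, in the T2 column, which the table note defines as "immediately after last session".

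Three other statements bear on the consequence. The course is "10 sessions in total". The section on inclusion and exclusion criteria says that "patients have the right to leave the study", and also: "In case of any significant adverse effects (AEs), the procedures for the respective patients will be terminated".

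**The concern.** AEs and tolerability are part of the stated aim of the study, and the article presents the multisession course as the reason for studying them. The two schedules collect different data. A form at each session shows what was felt, when it was felt and whether it grew over the course. A form at the end of the course gives one recalled summary, and as written it is not scheduled for a patient who does not reach the end. Because the protocol ends procedures for significant AEs, the patients without a form could include those whose AEs matter most. Staff working from the outcomes section and the assessment schedule would apply the weaker rule without knowing that the Methods section sets another.

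**Working it through.** No figure in the plan needs reproducing. The check is a comparison of text, with simple arithmetic for scale.

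**1. Is it the same instrument?** Yes. Both sections on adverse effects refer to the customized questionnaire in Supplementary File 1, so these are not two forms with separate schedules.

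**2. Where is the mark in Table 2?** After the row label, the columns run: enrolment, allocation, T1, intervention, T2, T3, T4, T5. The AE mark is in the fifth, T2. As a check on the count, the THI row has marks in the third, fifth and eighth columns (T1, T2, T5). This agrees with the text, which measures THI before the intervention, immediately after it and at one month.

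**3. The schedules side by side.**

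| Place | Timing of the AE form |
|---|---|
| Abstract | after each session |
| Methods, adverse effects | during and after each session |
| Outcomes, adverse effects | after the last session |
| Table 2 | T2 (after the last session) |

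The first two differ slightly, since one includes assessment during the session. The conflict that matters is between the first two and the last two.

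**4. Scale.** Counting post-session records for patients who complete the course:

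- Per patient: 10 sessions × 1 = 10 records, against 1.
- At n = 90, the total in the Abstract: 10 × 90 = 900, against 90.
- At 25 per group, the figure in the sample size section: 3 × 25 = 75 patients, so 10 × 75 = 750, against 75.

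The ratio is 10 to 1 whichever total is used.

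**5. What happens to a patient who stops early?** Take a patient who stops after session 3. Under the Abstract and Methods rule there are three post-session records, including the session that led to stopping. Under the outcomes section and Table 2, read literally, none is scheduled. The rule on terminating procedures implies that someone notices significant AEs during the course, but it sets no recording schedule.

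**6. Can worsening over sessions be seen?** This needs at least two time points within the course. The end-of-course schedule supplies one.

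**The case against.** The strongest reply is that the outcomes section is loosely drafted and no end-only design was intended. Neither that section nor Table 2 excludes earlier forms. A form after session ten is also what the per-session rule would produce on that day, so the T2 mark is compatible with both schedules. The per-session rule is stated twice, once with a reason. This is a fair account of what was probably meant, and it supports choosing the per-session rule. It does not remove the conflict: the outcomes section gives a complete timing statement for the same form, and it differs.

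The blank Intervention cell in the AE row is weak evidence. The two stimulation rows are unmarked in that column too, although stimulation must take place there, so marks may have been lost or never entered. The point does not depend on that cell.

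The last session could also mean each patient's own last session. That would reduce the loss among early stoppers, but the article does not say so, and earlier sessions would still depend on recall.

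Two stronger readings are tempting and not supported. First, the increase from 22 to 25 patients per group (3/25 = 12%) might be taken to show that some 9 (12% of 75) to 11 (12% of 90) patients would lack a form. But the allowance is not a forecast of stopping before session ten. The article attributes attrition to the length of the course and not to AEs, and the range applies one allowance to two inconsistent totals. Second, a reader might conclude that harm in the active arms would be understated. The documents give no AE or dropout rates by arm, and the termination rule applies to all arms, so this is a possibility and not a demonstrated bias.

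**Conclusion.** The inconsistency is explicit and real. If the outcomes section and Table 2 are followed, patients who leave or are stopped before session ten may have no AE form, the others must recall ten sessions at once, and a trend over sessions cannot be examined. AEs could therefore be under-recorded. The documents fix the contrast in planned records (10 to 1 per completing patient), but not the number of patients affected or the direction of any bias between arms.

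The loss among early stoppers assumes that the last session means session ten and that no per-session form is completed. Severity is moderate: a stated aim is affected, but the primary outcome, the sample size and the efficacy analyses are not.

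**What to change.** Reconcile the Abstract, both sections on adverse effects and Table 2 on the per-session rule.

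- In the outcomes section, say that the questionnaire is completed after each session, including the last session attended by a patient who stops early.
- In Table 2, mark AE and tolerability assessment across the intervention sessions as well as at T2.
- Use the same wording in the Abstract and Methods on whether the form is also completed during the session.
- State that the AE summary includes everyone who received at least one session.

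The cost is a few text edits. Patients already attend daily during each treatment week, and the Methods section already plans the per-session form. The Trial status section says allocation is still to come, so at the time of writing the correction could be in place before the first stimulation. Effects not recorded at the session cannot be reliably recovered later.

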## Statistical assessments

All statistical tests will be performed using
SPSS (V20.0, IBM Corporation, New York, USA). To determine whether the anodal, cathodal, and sham tDCS groups are well-matched in terms of age, sex, quality of tinnitus, tinnitus laterality, THI score, and duration and class of hearing loss, these dependent variables will be compared between the three groups using independent samples t-tests.

For nominal data like gender and class of hearing loss, Chi-square tests will be conducted across groups. Independent sample t-tests were also used to determine if individual baseline measures differed between groups (THI, tinnitus loudness, and distress). Prior to conducting
*t*-tests, Levene’s test for equality of variances was used. In no instance was Levene’s test violated; thus, equality of variances was assumed. The number of female and male participants and the quality of tinnitus symptoms, across each group will be compared using Pearson Chi-square tests. Mixed repeated-measure ANOVAs with the within‐subject factor time and the between‐subject factor stimulation were performed for evaluating changes in THI, tinnitus loudness, tinnitus distress, BDI and BAI scores. For the ANOVAs, sphericity was tested with the Mauchly’s test, and in the event of a violation of Mauchly’s test, the Greenhouse-Geisser correction was applied. In case of significant effects, follow-up post-hoc t-tests were carried out using LSD adjustments for multiple comparisons to examine if tDCS caused a significant difference relative to sham or baseline. An analysis of covariance will be performed with Time as within-subject factor, Stimulation as between-subject factor, and gender, laterality of tinnitus, duration of tinnitus as covariates. In addition, we will calculate Pearson’s correlations between change of THI and tinnitus loudness and distress values from pre- to post-stimulation.

Finally, we will examine the number of responders versus non-responders under each treatment condition (anodal, cathodal, and sham). This will be accomplished by calculating change scores between the pre-treatment and post-treatment THI values (Pre-treatment – Post-treatment). Responders will be considered individuals who showed reductions in THI score of equal or more than 20 points in the THI score (Pre-treatment THI – Post-treatment THI ≥ 20). For tinnitus loudness and distress a 10 percent or 2-point reduction of 0–10 scale is considered as treatment response. Pearson’s chi-square tests will be used to evaluate whether there are differences in the proportion of responders versus non-responders under each condition. For all statistical tests the P-value < 0.05 is defined as statistically significant level.

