^29^. The THI is widely used as the primary outcome measure in double-blind trials with a control group to assess the effect of pharmacological or non-pharmacological agents in tinnitus patients. The functional subscale items reflect the effect of tinnitus on mental, social, occupational, and physical functioning. The emotional subscale items probe the individual’s emotional reactions to the tinnitus and the catastrophic response items address whether tinnitus makes the respondent feel desperate, trapped, hopeless or out of control. In this study, the THI will be assessed prior to intervention, and immediately, and at one month after the last tDCS session. Response to treatment is defined as a reduction of equal or more than 20 points in THI score (Pre-treatment THI – Post-treatment THI ≥ 20). This cut-off value for treatment response to tDCS is generally considered as significant clinical improvement in the previous similar studies
^15,
30^. 

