## Sample size calculation

The sample size of this study was calculated using the standard sample size formula (represented in
Equation 1). The study of Shakhawat
*et al.* was considered as the basic study to determine the sample size of our study with the predetermined power and level of significance. Considering the power of 85 percent and for confidence interval of 95 percent, the sample size of this study is 22 patients. We will use 25 patients in each group so that future attrition of the patients due to long term period of the tDCS sessions will be compromised.

$$n=\frac{{\left(z_{1–\frac{\alpha }{2}}+z_{1–\beta }\right)}^{2}(S_{1}^{2}+S_{2}^{2})}{{\left({\bar{X}}_{1}-{\bar{X}}_{2}\right)}^{2}}\;Equation\;1$$

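### The THI analysis treats baseline as an outcome level, adjusts for it in no efficacy model, leaves the deciding test unnamed and implies complete cases

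*Protocol article*

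**What the plan says.** All references are to the protocol article.

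- **Visits.** Under Outcomes assessments, "the THI will be assessed prior to intervention, and immediately, and at one month after the last tDCS session". These are T1, T2 and T5 in Table 2.
- **Model.** Under Statistical assessments, mixed ANOVAs with time within and stimulation between subjects "were performed for evaluating changes in THI, tinnitus loudness, tinnitus distress, BDI and BAI scores". If Mauchly's test is violated, "the Greenhouse-Geisser correction was applied". The software is "SPSS (V20.0, IBM Corporation, New York, USA").
- **Follow-up tests.** After any significant effect, LSD t-tests are used "to examine if tDCS caused a significant difference relative to sham or baseline". Which effect must be significant is not said.
- **Covariates.** The ANCOVA keeps time as a within-subject factor and takes "gender, laterality of tinnitus, duration of tinnitus as covariates". Baseline THI appears in the same section only in t-tests of whether the arms match. The Background lists it among the characteristics whose association with response is of interest.
- **Attrition.** Sample size calculation raises 22 to 25 per group for "future attrition of the patients due to long term period of the tDCS sessions". Inclusion and exclusion criteria says that after significant adverse effects "the procedures for the respective patients will be terminated".

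**The concern.** Three features of the written analysis work against the trial's main question, which is whether active stimulation lowers THI more than sham does.

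1. **Baseline is in the outcome.** No treatment effect can exist at T1, so a stimulation main effect averaged over T1, T2 and T5 is pulled toward zero. Baseline THI is collected, yet it is never used as a covariate to gain precision or to correct chance imbalance under non-stratified randomisation.
2. **The deciding test is open.** A significant time effect alone would license within-arm comparisons with baseline. Those are not randomised comparisons: natural fluctuation, regression to the mean and placebo response all enter them.
3. **Complete cases are implied.** Classical repeated-measures ANOVA with Mauchly's test and the Greenhouse-Geisser correction needs every level of time for each patient. A patient seen at T2 but not at T5 would leave the THI analysis altogether.

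At stake are precision in a trial of 25 to 30 per arm and a clear answer to which p-value decides efficacy.

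**Working it through.** **1. The plan's own figure.** Equation 1 with 85% power and two-sided α = 0.05 gives 22 per group, but the article states no means or SDs, so 22 cannot be reproduced from its inputs. Solved backwards, d = √(2 × (1.960 + 1.036)² / 22) = 0.90. The allowance from 22 to 25 is 1 − 22/25 = 12%. The article also gives n = 90 at 1:1:1, which is 30 per group. That conflict is a separate matter; the pairwise calculation below uses 25 and then 30.

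**2. Variances.** Let r be the correlation between visits (not stated; assumed 0.5 to 0.8), with SD 1 at each visit. The variance per patient is:

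- raw post score: 1
- change from baseline: 2(1 − r)
- baseline-adjusted post score: 1 − r²
- mean of three visits (stimulation main effect): (1 + 2r)/3, with only 2/3 of the effect retained

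Baseline adjustment relative to change is (1 − r²)/(2(1 − r)) = (1 + r)/2, that is 0.75 at r = 0.5 and 0.90 at r = 0.8.

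**3. Pairwise power.** With a true effect of 0.6 SD (assumed) and 25 per arm, power = Φ(effect/√(2 × variance/25) − 1.96).

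| r | Raw post | Change | Baseline-adjusted | Main effect |
|---|---|---|---|---|
| 0.5 | 56.4% | 56.4% | 68.8% | 41.0% |
| 0.6 | 56.4% | 66.0% | 75.5% | 37.9% |
| 0.7 | 56.4% | 78.2% | 84.4% | 35.2% |
| 0.8 | 56.4% | 91.8% | 94.2% | 33.0% |

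Against change, adjustment gains about 12, 10, 6 and 2 points. Against the main effect it gains about 28 to 61 points. With 30 per arm and r = 0.6 to 0.8 the order is the same: 64% raw, 74–96% change, 83–97% adjusted, 38–44% main effect.

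**4. The time × stimulation test, by simulation.** There were 3,000 runs with three arms of 25, three visits, equal correlation between visits, both active arms shifted 0.5 SD at both post visits, and no missing data.

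| r | Time × stimulation | ANCOVA at one month | Main effect |
|---|---|---|---|
| 0.5 | 41.5% | 50.4% | 28.6% |
| 0.7 | 65.5% | 68.8% | 24.0% |
| 0.8 | 85.0% | 85.0% | 22.9% |

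The interaction test gives up about 9, 3 and 0 points. It uses both post visits, whereas this ANCOVA uses one. With no true effect the interaction test rejected in about 5% of runs, both with complete data and after random deletion of patients.

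**5. On the plan's implied effect.** If d = 0.90 is on the change scale with 22 per group, the change contrast has 85.0% power. Adjustment gives 93.3% (r = 0.5), 90.1% (0.7) and 88.5% (0.8).

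**6. Complete cases.** Assume 5% missing independently at each post visit. THI loses 1 − 0.95² = 9.8%, leaving about 22.6 of 25. Loudness and distress lose 1 − 0.95⁴ = 18.5% over four post visits, or 1 − 0.95³ = 14.3% if T2 and T3, one hour apart, count as one contact. On d = 0.90, a 20% loss from 25 leaves 20 patients and 81.5% power.

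**The case against.** The strongest reply is that this is a conventional and valid analysis. The ANOVAs are said to evaluate changes, which points to time × stimulation rather than the main effect. That test compares randomised groups on change from baseline, and its type I error holds. The ANCOVA keeps time within subjects, so baseline THI already sits in the outcome vector. All of this stands. It is why the efficiency loss is modest and vanishes at high correlation in the simulation. It does not settle which significant effect triggers the post-hoc tests, nor what quantity the tests against sham compare. Raw scores are the natural reading, but the article does not say so.

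A reader might infer that the plan breaks the randomised comparison. The document does not support that. Complete-case analysis would bias the interaction only if missingness relates to arm or outcome. The part that is not a randomised comparison is the within-arm test against baseline.

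A reader might also infer that the plan states that patients with a missed visit are dropped. It does not. Deletion follows from the named method, and a missing-data rule may stand in a document not shown. The article ends procedures after significant adverse effects but does not say that assessments end, and it nowhere mentions stopping for lack of benefit. A completers' bias favouring the active arms is therefore conjecture. The THI loss at 5% missing per visit is also covered by the increase from 22 to 25.

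**Conclusion.** The point holds as an efficiency and clarity defect in a method that the article fixes in writing. Baseline THI is an outcome level, it is a covariate in no efficacy model, and the deciding test is not named. Against the time × stimulation test the loss is about 0 to 9 power points in simulation, and about 2 to 12 for a pairwise change contrast. It becomes large only if the stimulation main effect or raw post scores decide. These sizes rest on an assumed correlation of 0.5 to 0.8, assumed effects of 0.5 or 0.6 SD, and equal correlation between visits; the article gives none of these. Complete-case analysis is implied, not stated. Its cost for THI is small at low missingness and grows beyond the 12% allowance. The change should be made, but the planned interaction test would not be invalid without it.

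**What to change.** - Replace the mixed ANOVA for THI by a linear mixed model (SPSS MIXED) on T2 and T5, with arm, visit, arm × visit and baseline THI as covariate.
- Analyse patients in their assigned arm with whatever post-baseline visits they have. A patient with no post-baseline THI still contributes no outcome, so report their number by arm.
- Name the contrast of each active arm with sham, at one visit fixed in advance, as the efficacy test. The article does not choose between T2 and T5; the sponsor must.
- Drop within-arm tests against baseline as evidence of efficacy; they may remain descriptive.
- Use the same model for loudness and distress, each with its own baseline.

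The cost is analysis wording only: the software and data are already planned. The Trial status section reports that allocation had not yet taken place, so the change could precede any outcome data. Continued follow-up of patients who stop stimulation would be an operational commitment beyond this fix, with its own cost.

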### Study protocol

This study is a double-blind randomized controlled clinical trial design and patients will be randomly assigned into three groups of anodal and cathodal tDCS and sham tDCS. The random allocation will be performed based on balanced randomization [1:1:1] where the allocation concealment will be applied by random allocation cards using computer-generated random numbers. The three groups will be matched for age, gender, ethnicity, and audiometric main characteristics. To reduce the procedure and subjective bias, the patients, the researchers who will evaluate the outcomes, and the researchers who perform data analyses will be blinded on the type of protocol. In addition, the blinding quality of the study will be assessed after completion of the intervention.

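### LSD is called a multiplicity adjustment but adjusts nothing; the post-hoc tests have no defined trigger, cover two unranked THI time points, and let change from baseline be read as a tDCS effect

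*Protocol article*

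**What the plan says.** The Statistical assessments section fits a mixed repeated-measures ANOVA with time and stimulation as factors to THI, loudness, distress, BDI and BAI. Where this gives significant effects, without saying which, post-hoc t-tests follow, "using LSD adjustments for multiple comparisons to examine if tDCS caused a significant difference relative to sham or baseline". The same section sets one threshold: "For all statistical tests the P-value < 0.05 is defined as statistically significant level".

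Under Outcomes assessments, "Tinnitus handicap inventory (THI) score will be the primary outcome", and "the THI will be assessed prior to intervention, and immediately, and at one month after the last tDCS session". THI therefore has two post-treatment values, T2 and T5, and neither is named as primary. The responder analysis works by "calculating change scores between the pre-treatment and post-treatment THI values" and does not say which of the two is the post-treatment value.

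The Sample size calculation section uses a formula for one comparison of two means at 85% power and 95% confidence. It gives 22 patients, raised to 25 per group for attrition.

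**The concern.** Three features of one sentence combine.

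- **The label is wrong.** LSD applies ordinary pairwise t-tests at the nominal level. The only protection it offers comes from a preceding F test. With three groups at one time point that protection is complete. It does not extend to several time points, or to an F test on a different question.
- **The trigger is undefined.** The ANOVA yields a time effect, a stimulation effect and an interaction, and the text does not say which one opens which tests. If a time effect alone opens the comparisons with sham, an improvement common to all arms removes the protection.
- **Baseline stands beside sham as a reference for causation.** A pre-post change within an active arm contains placebo response, natural course and regression to the mean. The Discussion presents control of placebo effects as the main advantage of the design, and a within-arm test makes no use of it.

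At stake is the main conclusion. An arm could be reported as effective on the better of two time points, or on a change that sham patients show equally.

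**Working it through.** **Inputs from the protocol:** three arms, 1:1:1; THI at T1, T2 and T5; 0.05 for every test; 25 per group (Sample size calculation) or 90 in total, i.e. 30 per group (Abstract). **Assumptions, not in the protocol:** THI SD 20, correlation between visits 0.6 or 0.8, compound symmetry, normal data, and an equal improvement of 0, 5 or 8 points in all arms (0, 0.25 or 0.40 SD).

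**1. The plan's own figure.** The means and SDs behind n = 22 are not given, so it can only be inverted. With n = 2(z₀.₉₇₅ + z₀.₈₅)²/d², d = √(2 × (1.960 + 1.036)²/22) = 0.903. This covers one two-group test at 0.05 and makes no allowance for multiplicity.

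**2. Independence reference.** Two active arms at two times give four tests against sham: 1 − 0.95⁴ = 18.5%. For one arm at two times: 1 − 0.95² = 9.75%. Correlation between the tests lowers both.

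**3. Simulation, no tDCS effect** (25 per arm, 10,000 trials per scenario, post-hoc tests opened by any significant ANOVA effect):

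| Correlation | Shared improvement | Any false active-vs-sham result, T2 or T5 | Any active arm different from baseline |
|---|---|---|---|
| 0.6 | 5 points | 12.7% | 56.8% |
| 0.6 | 8 points | 14.8% | 93.2% |
| 0.8 | 5 points | 13.3% | 85.4% |
| 0.8 | 8 points | 13.9% | 99.8% |
| either | none | 5.7-6.3% | about 6% |

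**4. Same settings, other triggers.** If only a stimulation or interaction effect opens the tests against sham, the false-positive rate is 4.9-5.8% whatever the shared improvement. If only the interaction does, it is 1.1-1.7%.

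**5. One arm works (0.9 SD), the other equals sham.** The inactive arm is falsely significant against sham at T2 or T5 in about 8-9% of trials, even with the interaction as the only trigger. The working arm makes the interaction significant almost always, so the inactive arm faces two unadjusted tests; the ceiling is the 9.75% of step 2.

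**6. Sensitivity.** With a shared improvement of 0.3 or 0.5 SD, correlations of 0.5 to 0.85 and 25 or 30 per arm, the any-effect trigger gives 13-17% false results against sham, and 63-100% of trials with an active arm different from baseline. The 75-versus-90 discrepancy in total sample size does not change the picture.

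**The case against.** The strongest reply is that the text does not say a time effect opens comparisons with sham. By common convention a time effect opens contrasts over time, and a stimulation or interaction effect opens contrasts between arms. On that reading, error stays near 5% when neither arm works. This stands: 13-15% is conditional on one reading of an unspecified rule. It does not remove the 8-9% for an inactive arm when the other arm works, which comes from the two time points.

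A second reply is that 57-100% is not a false-positive rate. In the simulation every arm truly improves, so the within-arm test is right to detect a change. This also stands. The figure shows how easily the baseline comparison turns positive, and becomes an error only if the change is attributed to stimulation.

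A reader might infer that the plan discards the sham control, or treats a change from baseline as sufficient proof of efficacy. The protocol does not support that. It sets no such success rule, the time-by-stimulation ANOVA is a between-arm model, and the responder test compares all three arms.

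On responders, the Abstract separates post-intervention from the one-month follow-up, which points to T2. The Outcomes assessments section uses post-intervention for T2 through T5, so the ambiguity remains. An unseen analysis plan might rank the time points. It would still have to correct the description of LSD and the causal wording about baseline, which are stated here and not merely left out.

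**Conclusion.** The concern holds as a fault in a stated rule. LSD is misdescribed as an adjustment, its trigger is not tied to a between-arm effect, two THI time points compete, and the wording allows an uncontrolled change to support a causal statement.

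The size is conditional. Active-versus-sham error under no effect lies anywhere from about nominal to about 15%, depending on which ANOVA effect opens the tests and on how much all arms improve. The 8-9% for an inactive arm does not need the permissive trigger; it assumes that the other arm works at about 0.9 SD. SD, correlation and shared improvement are assumptions throughout. That LSD adjusts nothing, and that a baseline comparison cannot separate tDCS from placebo, needs none of them.

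**What to change.** 1. Rest causal and efficacy claims only on anodal versus sham and cathodal versus sham for THI at one named primary time point. T5 is a natural candidate because the protocol stresses the one-month follow-up, but it is one valid choice among several. Use the same time point for the THI responder rule.
2. Control the familywise error by Holm or Dunnett, or by LSD opened only by a significant three-group between-arm F test at that time point. The latter is valid: if all three arms are equal, the F test limits the error to 5%; if only one pair is equal, a single true null is tested at 5%.
3. Make the other time point and anodal versus cathodal secondary.
4. Report changes from baseline descriptively, without causal wording.

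**Cost.** This is analysis wording, and the Trial status section says allocation had not yet taken place. There is a price in power. At the back-solved d = 0.903, power for a two-sided test at 0.025 is Φ(d√(n/2) − 2.241) by the normal approximation of Equation 1: Φ(2.996 − 2.241), about 77%, with 22 evaluable per arm; Φ(3.194 − 2.241), about 83%, with 25; and Φ(3.499 − 2.241), about 90%, with 30. For 85%, 27 per arm are needed. If Holm or Dunnett is chosen, the stated 85% at n = 22 should be restated. The F test followed by LSD avoids most of this loss when the other active arm is either inert or equally effective, and less of it when that arm's effect lies in between.
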